## Control

Participants randomised to the control group will receive only the study assessments and continue with their standard care. This is so that in the definitive trial the impact of the intervention over and above standard care can be evaluated.

## Measures

Measurement timepoints for the pilot are baseline (T0) and 3 months (T1; operationalised as 12–16 weeks from randomisation). When a participant provides consent they will be sent URL links to online questionnaires via email (with the option to complete these by phone with a researcher if they experience difficulties), and mailed weighing scales (Seca 803 if they weigh less than 150kg and Seca 813 if they weigh over 150kg), a tape measure (Seca 201), and an activPAL4micro accelerometer (PAL Technologies Ltd., Glasgow, UK).

### Sociodemographic & disease characteristics (T0)

Details of each participant’s cancer diagnosis, treatment(s), and other health conditions (including previous cancer diagnoses) will be recorded from their hospital medical notes.

In the online questionnaires, participants will report their age, gender, employment, education, marital status, living arrangements, and ethnicity. Participants will be asked to self-report details of their cancer diagnosis, treatment, and other comorbid health conditions. This is to capture any further health information that is not included in the hospital medical records (e.g. information that would otherwise be included in GP records, or records from other hospitals). Participants’ postcodes will be used to determine socioeconomic position (Index of Multiple Deprivation) [60].

### Physical activity (T0 and T1)

Physical activity will be measured using thigh-worn activPAL4micro accelerometers that participants will be asked to wear continuously for seven days (PAL Technologies Ltd., Glasgow, UK). The activPAL protocol, which follows published recommendations for using the device and expert advice from the Trial Steering Committee, includes waterproofing the device using specially designed nitrile sleeves and waterproof dressings, asking participants to wear it continuously, and including the data for analysis if 3 days of data are available [61]. Participants will be mailed instructions on how to wear the device, a log-sheet to record when the device was worn and bedtimes and waketimes, and a freepost envelope to return it. The primary outcome of the future full RCT will be activPAL-assessed average daily brisk walking (> 100 steps/min). The activPAL has shown excellent reliability and validity in measuring step number and cadence (steps/minute) and has been used in other studies with people LWBC and clinical populations [62, 63]. Other physical activity outcomes that will be explored are total daily steps, minutes of light physical activity, standing time and sitting time.

Participants will also complete the Godin Leisure-Time Exercise Questionnaire (GLTEQ) [64], which has demonstrated favourable validity and reliability against objective measures of physical activity and is widely used in oncology research [64, 65]. The questionnaire will be adapted to add a question about duration of activities to allow calculation of minutes of MVPA, in addition to the leisure score index, a practice that is common in oncology research [65].

### Anthropometric outcomes (T0 and T1)

Participants’ height, weight (without outer clothing/shoes on) and waist circumference (at umbilicus) will be measured by participants in their own homes using the study weighing scales and measuring tapes provided. Written instructions will be included to help participants complete these measurements accurately. Studies suggest that self-reported weight is sufficiently reliable and accurate where objective measurement is not feasible [66, 67]. BMI will be calculated using the standard formula of weight (kg)/height (m)^2^. Self-measured waist circumference is also appropriate for large-scale studies where objective measurement is not feasible [68].

### Well-being (T0 and T1)

Health status will be measured using the five-level EuroQol-5D questionnaire (EQ-5D-5L), which has established reliability and validity from a review of 12 studies of cancer patients [69]. This will be used to generate quality-adjusted life years (QALYs) to facilitate the cost-effectiveness analysis.

Cancer-specific quality of life will be measured using the Functional Assessment of Cancer Therapy-General (FACT-G) scale [70]. The FACT-G is a 28-item questionnaire that has excellent test-retest reliability (*r* = .92) and has been validated against the Functional Living Index-Cancer (FLIC) (*r* = .79) [70, 71].

Fatigue will be measured using the 13-item fatigue subscale of the Functional Assessment of Chronic Illness Therapy-Fatigue (FACIT-F) (previously Functional Assessment of Cancer Therapy-Fatigue (FACT-F)) questionnaire [72]. The 13-item fatigue subscale of the FACIT-F has excellent test-retest reliability (*r* = .90), internal consistency (*α* = .93–.95), and has been validated against the Profile of Mood States (POMS) fatigue (*r* = − .74), POMS vigour (*r* = .66) and Piper fatigue (*r* = − .75) [72–74].

Sleep quality will be assessed using the Pittsburgh Sleep Quality Index (PSQI), an 18-item questionnaire that assesses sleep quality and disturbances over a 1-month time interval [75]. The PSQI has been used extensively and has good psychometric properties in both clinical (including cancer) and non-clinical samples [76]. In women with breast cancer, the PSQI has been demonstrated to have high internal consistency (*α* = .80) and good validity when compared against related constructs such as sleep problems (in the Symptom Experience Report; *r* = .65) and sleep restlessness (in the Center for Epidemiological Studies Depression Scale; *r* = .69) [77].

Anxiety will be measured with the Generalised Anxiety Disorder Assessment (GAD-7), which has good test-retest reliability (*r* = .83), excellent internal consistency (*α* = .92), and has been validated against the Beck Anxiety Inventory (*r* = .72) [78]. Depression will be measured with the Patient Health Questionnaire (PHQ-9), which shows adequate diagnostic accuracy in cancer patients [79–81].

Physical activity self-efficacy will be measured using the Physical Activity Appraisal Inventory (PAAI), which has demonstrated excellent reliability in women with breast cancer (*α* = .96) [82]. The PAAI also has established validity [82]. Self-efficacy to self-manage cancer will be measured using the Cancer Survivors Self-Efficacy Scale (CS-SES), an 11-item questionnaire with excellent reliability (*α* = .92) [83].

Habit strength for walking (‘going for a walk’ and ‘walking briskly’) will be measured with the Self-Report Behavioural Automaticity Index (SRBAI), which has established reliability and has shown to be sensitive to hypothesised effects of habit on behaviour [84].

Health and social care service use will be measured using the Client Service Receipt Inventory (CSRI), which has been validated against objective primary care records and is also recommended for usage of hospital and other community health services [85].

### App use (T1)

Participants in both groups will also be asked to report their usage of any physical activity app, or any other attempts to change their physical activity, during the study period, and asked what prompted them to do this. Intervention group participants will be asked to complete brief intervention feedback questions (including a self-report question of whether they ever downloaded Active 10) and will be asked to self-report their usage of Active 10 throughout the study period (never, once, less than monthly, monthly, fortnightly (every 2 weeks), weekly, 3–4 times per week, almost every day or every day). Intervention participants will also be asked to complete questions from the Digital Behaviour Change Interventions Engagement Scale [86].

### Timing of physical activity (T1)

In a definitive trial, we would conduct an exploratory analysis using the activPAL data alongside habit strength to investigate whether those who walk in the morning have higher habit strength than those who walk in the evening. Previous research suggests that habits form quicker in the morning than the evening [87]. Chronotype (individual differences in sleep timing and in preferences for a given time of day) will be considered a covariate in this analysis and assessed using a sub-scale of the Morningness-Eveningness questionnaire (MEQ) [88, 89]. This sub-scale has been found to be reliable and to correlate well with the full scale [90].

### Qualitative interviews (decliners at T0 and participants at T1)

To further understand how a future intervention could be designed to be as inclusive as possible, individuals who decline to participate will be asked to briefly provide reasons if they are willing. They will also have the option to consent to participate in an interview to further explore reasons, and up to 30 interviews will be conducted. This method has been utilised succesfully in an ongoing exercise trial with myeloma patients [63].

Interviews will also be carried out at the end of the trial with any participants who agree to be interviewed. The interviews will take place after a participant has completed all other data collection at T1 and will be conducted to explore experiences of participation, being randomised, and views on providing permission to access NCRAS/HES data. Intervention arm participants will also be interviewed about their experiences of using the app, the intervention materials, and their perceptions of app usage and engagement. Participants will be invited to submit photographs of the places that they walk. This is optional, but if participants consent, they will be able to upload pictures to a secure website along with brief details of where the photograph was taken, why they were walking there, how long they walked and any additional details they wish to share. Photographs will be used to prompt discussion about the environments chosen for brisk walking. This method of photo-elicitation has been used to understand walking environments in previous work and led to a more in-depth understanding of barriers and facilitators to walking [91]. All interviews will be semi-structured and based on a topic guide, take place via telephone, and will be audio-recorded and transcribed verbatim.

## Statistical analysis

Baseline comparability of the randomised groups will be assessed using descriptive statistics (e.g. age (continuous), gender (categorical), key outcome measures (e.g. physical activity participation)). The outcomes outlined in Table 1 will be reported descriptively. Any reasons provided for declining not covered in the specific outcomes will also be reported, as well as details of answers provided to the feedback questionnaire, within the intervention group. Mean and standard deviation estimates for the intended primary outcome measure at 3 months (activPAL measured average daily minutes of brisk walking (> 100 steps/min)) will be calculated and reported descriptively. These results will be used to inform a sample size calculation for the future definitive trial.

An initial economic evaluation will be conducted to provide an estimate of the potential cost-effectiveness of the intervention. QALYs will be estimated based upon the EQ-5D-5L combined with standard valuation sources [92, 93]. Costs will include the costs associated with the intervention (promotional materials, time spent delivering the intervention recommendation) and other NHS resource use measured using the CSRI. Costs and QALYs will be combined in an analysis to estimate the incremental cost-effectiveness ratio (ICER) associated with the intervention compared to the control group. Uncertainty in the results will be characterised using cost-effectiveness planes and cost-effectiveness acceptability curves [94]. A value of information analysis will also be conducted at this stage. The expected value of perfect information (EVPI) and expected value of perfect partial information (EVPPI) will be estimated.

## Qualitative analysis

Qualitative interviews will be analysed thematically using an approach that is both deductive and inductive, to ensure that the full range of participants' responses are represented, following the steps outlined by Braun and Clarke [95]. These findings will add more in-depth understanding to the feasibility and acceptability analysis described above.

## Ethical considerations

The trial protocol has been approved by the Yorkshire & The Humber - South Yorkshire Research Ethics Committee (21/YH/0029) and by the Health Research Authority. The Research and Development Department at the study site has also authorised the study to go ahead following a capacity and capability review. Potential amendments to the protocol will only be implemented if ethical and regulatory approval, including NHS permission where required, is obtained.

### Consent

Consent from each participant prior to participation in the trial will be collected online through REDCap hosted within UCL’s Data Safe Haven (details below) [96]. All participants will be informed that they are under no obligation to enter the trial. All participants will also be informed that they can withdraw at any time during the trial without having to give a reason, and that withdrawal will not affect the medical care they receive.

### Confidentiality

This study has been registered for Data Protection at UCL Records Office (Reference: Z6364106/2020/10/29). All data will be handled in accordance with the General Data Protection Regulation (2018) and the UK Data Protection Act (2018). Personal data will only be collected if it is deemed essential for the study. Wherever possible, personal data that has been collected will be pseudoanonymised. No identifiable personal data will be used in dissemination of the research.

### Adverse event reporting

All adverse events (AEs) and serious AEs (SAEs) that the research team become aware of will be assessed for severity, causality, and seriousness. All AEs and SAEs will be recorded. All SAEs will be reported to the sponsor. Events that are unexpected and thought to be related to the intervention will be reported to the Health Research Authority. In this population, a range of SAEs would be expected that relate to their cancer diagnosis and treatment, including episodes of acute illness, infection, new medical problems, and deterioration of existing medical problems. These could result in hospitalisation, permanent disability or incapacity, or death. These would not however be related to the intervention. There is one potential expected AE related to participation in the study; participants might experience mild skin irritation from the adhesive dressing when wearing the activPAL device as this has been observed previously in older adults [97].

### Data monitoring

The sponsor of this trial is UCL. A Trial Management Group (TMG) consisting of the Chief Investigators (AF and PL) and research staff employed on the grant (FK and CM) will be responsible for overseeing the trial. An external Trial Steering Committee, including two independent members, the trial co-investigators, and a lay representative will meet once-twice per year (alongside the TMG) and will provide overall supervision of the trial. There will be no formal data monitoring committee and no criteria have been set for stopping the study early as this is a pilot study and walking is a very low-risk intervention.

### Data management

All study data will be stored securely within the UCL Data Safe Haven encrypted platform [91]. The Data Safe Haven is built using a walled garden approach where the data is stored, processed, and managed within a secure environment [91]. Only members of the research team will be able to access the dataset.

### Data archiving

All electronic research data will be stored securely within the UCL Data Safe Haven for 12 years after the trial end date, after which point the data will be completely anonymised (by removing the study pseudonym and deleting all contact details including proof of consent) [91]. The anonymised dataset will be entered into the UCL Data Repository and available here for at least 20 years from the trial end date. Other study-related documents will be archived at UCL and each participating site for 20 years from the trial end date and in line with all relevant legal and statutory requirements.

### Dissemination

The results of this study will be disseminated through peer-reviewed publications and conference presentations. The results will also be disseminated through social media outlets such as Twitter, and via our PPI representatives.

## Discussion

Conducting a pilot and assessing the feasibility of study procedures is an essential part of developing and evaluating complex interventions [98]. This pilot study follows recommendations to use both quantitative and qualitative measures to assess the feasibility and acceptability of the study design in as much detail as possible [98]. The definitive trial that will be run following revision to the current methodology, as required, will address the limited evidence base for theory-driven smartphone app-based interventions designed to promote physical activity in people LWBC. Yorkshire Cancer Research have awarded our group a grant to complete this pilot study and a larger trial, meaning that the definitive trial will be able to proceed quickly once the results of this pilot have been analysed.

The strengths of the intervention include its tailored and theoretically-informed approach to promote brisk walking, an activity that is perceived as safe, achievable, enjoyable, and sustainable by people LWBC [29]. The design of the intervention has been informed based on input from people LWBC. This intervention is accessible, low cost, and scalable, due to the use of an app maintained by Public Health England (or its successor bodies). It is hoped that the intervention could be replicated by a HCP as part of routine care for people LWBC, should it be implemented on a larger scale. A strength of the trial design is the use of objective physical activity measurement.

A limitation of the intervention is that it is only accessible to participants who own a smartphone. However, this intervention would be most appropriate for those who already have a smartphone and as these rates are increasing, this is becoming the majority of the population [23, 24]. We will collect data on how many participants are excluded because they do not own a smartphone so that this can be addressed in a future RCT if required. Another limitation is that the study is taking place in one hospital site in South Yorkshire, and thus it may be that the feasibility results do not generalise to all hospital sites. However, as this hospital is in a deprived area recruitment rates would likely be similar or better in other areas. Also, as the recruitment approach does not involve face-to-face contact with participants it is likely transferable across sites. It is possible that the intervention may be more or less acceptable in this area than others; however, if it is acceptable here, this would imply that it is acceptable to those most in need.

As the Active 10 app is publicly available it is possible that those in the control group could use it during the study. However, the intervention is a package that includes a recommendation to use this app alongside behavioural support to do so. Therefore, even if a control group participant does start using the app this is not equivalent to being in the intervention group. Patients have reported that they are keen for health professionals to recommend an app to them [29] therefore we think it unlikely that many of the control group will seek out the app on their own. We will assess this as a feasibility outcome.

To conclude, this pilot RCT will provide information regarding the feasibility and acceptability of testing this intervention to inform a future definitive RCT. The trial will also provide estimates of the parameters of the intended primary outcome measure for a sample size calculation for a future trial. Should the intervention be feasible, with or without adaptations, a future definitive RCT will aim to investigate the clinical and cost-effectiveness of the intervention among people affected by cancer.

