Digital interventions have potential for remote delivery of interventions, and smartphone apps are well-positioned as a platform due to their popularity and capabilities. Smartphone ownership continues to increase in all age groups; in 2021, 94% of adults aged over 55 in the UK owned a mobile phone, 83% of which were smartphones [23, 24]. Smartphone apps can track physical activity, deliver ‘in-the-moment’ behaviour change support, and, once developed, can be relatively cost-effective. A meta-analysis of 15 studies conducted by our group found that digital interventions could increase moderate-to-vigorous physical activity (MVPA) participation by approximately 40 min per week in people LWBC [25]. However, only two of these interventions were delivered via apps, and most were small pilot studies and used self-reported physical activity [25]. A subsequent review indicated that smartphone interventions may increase physical activity in people LWBC and that incorporating some element of personal contact could enhance efficacy [26]. This review also highlighted the importance of assessing cost-effectiveness [26]. In order for interventions to have a positive impact on long-term health, they need to promote behaviour change that will be maintained. One route to behaviour maintenance is establishing habits; behaviours which are cued by the contexts in which they are performed, rather than intentionally selected on each occasion they are performed [27]. Habit theory provides a basis on which to provide guidance to help people develop habits [28]. An additional consideration for app-based interventions is a need for sustainability beyond the end of research funding, so utilising/adapting publicly or commercially available apps could have potential.

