## Eligibility criteria

Participants will be eligible if they have a confirmed diagnosis of breast, prostate, or colorectal cancer at a single hospital site in South Yorkshire, are aged 16 years or older, own a smartphone that uses Android or iOS (Apple) operating systems, are able to provide informed consent, have access to a computer and an email address, and are willing to complete online questionnaires. This hospital serves an area of high deprivation where cancer incidence, mortality, physical inactivity, and obesity are all high compared to the English average [34, 35]. Participants aged 16 and 17 years of age are not excluded from participation as it has been found that this group are keen to be included in cancer research and have often been overlooked in previous research [36, 37].

Exclusion criteria are as follows: having localised disease and it has been more than 6 months since completion of radical treatment (i.e. surgery to remove cancer, radiotherapy, systemic therapy with curative intent), being unable to understand spoken/written English, having an Eastern Cooperative Oncology Group (ECOG) performance status ≥ 3, a diagnosed cognitive impairment (e.g. dementia), a cognitive and/or physical impairment that prevents participation in brisk walking, a clinician-estimated life expectancy of < 6 months, or are receiving end of life care, due to have surgery to remove cancer in the next 5 months, < 6 weeks after surgery to remove cancer, report already achieving 150 min of at least moderate-intensity physical activity weekly, report previous/current use of the intervention app, or report current or recent (< 6 months) participation in a health behaviour change study.

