## Recruitment and setting

Research nurses/members of the research team with contractual arrangements at the hospital site will search lists of current breast, prostate, and colorectal cancer patients and examine medical notes to identify potentially eligible participants. At least one clinician with responsibility for the patient’s care will review the list of potentially eligible participants and confirm whether a patient can be approached about the study.

Potentially eligible participants will be sent a letter informing them about the study. Participants who indicate interest will answer a telephone-based eligibility screening questionnaire. If eligible, participants will be sent an email with a link to the online participant information sheet and consent form (administered via REDCap electronic data capture tools hosted at University College London (UCL)) [40, 41]. The consent form (see Supplementary Material) includes asking for optional additional consent to access Hospital Episode Statistics (HES) and the National Cancer Registration and Analysis Service (NCRAS) registries to understand the willingness to consent to long-term follow-up of medical records. In this pilot, we will not access this data, but we ask participants to consent, as we would in a larger trial, in order to understand willingness to consent to this.

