Feasibility of administering the intervention	The percentage of the intervention group who: - receive a behavioural support call. - self-report successfully downloading the app.
Acceptability of the intervention	Percentage of participants who report that no aspect of the intervention (leaflet, call, planner, app) was useful. Percentage of withdrawals from intervention group compared to control group. Percentage of reasons for withdrawal relating to the intervention.
Retention rate	The percentage of participants, in each group, who complete any of the T1 follow-up assessment measures.
Acceptability of outcome assessments	The percentage of participants who consent who complete any baseline assessments. Completion rates, in each group, for each of the assessments at: - baseline - follow-up
Willingness of participants to consent to linkage with HES/NCRAS registries for long-term follow-up	The percentage of participants who consent for this aspect of the study.
Acceptability of online assessments	The percentage of participants who require help from a researcher to complete questionnaires. The percentage of potential participants who give this method of data collection as a reason for declining to participate.
Acceptability of providing informed consent online	The percentage of potential participants that state that they are unable/unwilling to provide consent online.
Self-reported app usage and engagement	Percentage of participants in the intervention group who report using the app for less than a month.
The proportion of screened participants ineligible and reasons for ineligibility	The number of participants screened and deemed ineligible for each inclusion/exclusion criteria.
Potential sociodemographic biases in recruitment	Anonymised aggregate socio-demographics (age, gender, ethnicity, Index of Multiple Deprivation, cancer type, cancer stage, time since diagnosis, treatment completed and started) of potentially eligible participants (from medical records and clinician approval) who did not participate in the trial compared with the study sample characteristics.
Fidelity of intervention delivery in the telephone/video calls	Average percentage of required behaviour change techniques covered in 25% of participants’ intervention calls (randomly selected) scored against a checklist.

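### The planned count of people excluded for lack of a smartphone is a lower bound, because ownership is asked only of people who have already shown interest

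*Protocol article*

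**What the plan says.** Under Eligibility criteria, participants must "own a smartphone that uses Android or iOS (Apple) operating systems".

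Recruitment and setting gives the order of events. Staff search patient lists and "examine medical notes to identify potentially eligible participants", and a clinician confirms who may be approached. Then "Potentially eligible participants will be sent a letter informing them about the study". After that, "Participants who indicate interest will answer a telephone-based eligibility screening questionnaire". The article mentions no check of smartphone ownership before the telephone step.

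Table 1 (Feasibility outcomes) defines the ineligibility outcome as "The number of participants screened and deemed ineligible for each inclusion/exclusion criteria".

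The Discussion promises the count and states its purpose: "We will collect data on how many participants are excluded because they do not own a smartphone", with a view to dealing with access in the later RCT if required. It gives no threshold.

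There is a second, voluntary route. The section on qualitative interviews says that people who decline will be asked for brief reasons if willing, and the Statistical analysis section says that reasons not covered by the specific outcomes will also be reported.

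**The concern.** The people counted are not the people about whom the question is asked. The question is how many otherwise suitable patients the smartphone criterion shuts out. The count covers those who replied with interest and were then found to have no smartphone. Someone who sees from the letter that the study concerns an app, and who has no device to run it, has little reason to reply. That person enters the results as not interested rather than as excluded.

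The other planned outcomes do not clearly recover these cases. Table 1 has decliner items for randomisation, online data collection and online consent, but none for lacking a smartphone. The comparison of participants with non-participants covers age, deprivation and clinical variables, but not ownership. The enrolment percentage is taken over people who are both interested and eligible, so non-owners are absent from it.

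At stake is how the pilot informs the definitive trial. The Discussion argues that acceptability at this deprived site would carry over to those most in need. That argument is weaker if the number removed by the smartphone criterion is understated and the figure is not marked as such.

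**Working it through.** The plan states no expected number of smartphone exclusions, so there is no figure of its own to reproduce. The check is how far the share of non-owners among those screened can differ from the share among those invited.

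**Inputs**
- q, the share of invited people without a smartphone. The Background says "94% of adults aged over 55 in the UK owned a mobile phone, 83% of which were smartphones". Read literally, ownership is 0.94 × 0.83 = 0.780, so q = 0.220. If the 83% is read as a share of all over-55s, q = 0.17. A value of q = 0.10 is added as an assumption, because the trial recruits from age 16.
- k, the non-owners' rate of reply divided by the owners' rate. The document does not give it. It is assumed here over a range from 1 to 0.

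**Formula**

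Share of non-owners among those screened = qk / (qk + 1 − q).

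Example with q = 0.220 and k = 0.5: 0.110 / (0.110 + 0.780) = 0.124.

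| k (assumed) | q = 22% | as a fraction of the true 22% | q = 17% | q = 10% |
|---|---|---|---|---|
| 1 | 22.0% | 1.00 | 17.0% | 10.0% |
| 0.75 | 17.4% | 0.79 | 13.3% | 7.7% |
| 0.5 | 12.4% | 0.56 | 9.3% | 5.3% |
| 0.25 | 6.6% | 0.30 | 4.9% | 2.7% |
| 0.1 | 2.7% | 0.12 | 2.0% | 1.1% |
| 0 | 0% | 0 | 0% | 0% |

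Two statements need to be kept apart. As a number of people, the screening count cannot exceed the number of non-owners invited, so it is a lower bound whatever k is. As a share of those screened, it is too low only if k is below 1.

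**Effect of the decliners' route**

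Suppose owners reply at 30%, k = 0.25 and q = 0.220 (all assumed except q). Per 100 invited, about 22 people are non-owners.
- Found by screening: 22.0 × 0.25 × 0.30 = 1.6.
- Not screened: 22.0 × (1 − 0.075) = 20.3.
- If a quarter of those not screened give the reason, the total found is 1.6 + 5.1 = 6.7.
- If half do, it is 1.6 + 10.2 = 11.8.

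The second route can therefore recover a substantial part of the shortfall. It depends on people responding at all and on the reason being recorded in a form that can be counted.

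**The case against.** The strongest reply has four parts.

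**Screening is not the only source.** Decliners are asked for reasons, up to 30 interviews with them are planned in order to make a later intervention more inclusive, and other reasons for declining are to be reported. This stands. A reader might infer that non-owners are counted only at screening, and the document does not support that. The route is voluntary, however, has no dedicated item in Table 1, and misses people who never answer.

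**The size rests on assumption.** This also stands. A reader might infer that the count will be far too low. With k = 0.75 the screened share is still 17.4% against 22%; a large shortfall needs k of about 0.5 or less, and nothing in the document gives k. The 22% is a national figure for over-55s, whereas this trial recruits from age 16 at one site with other access requirements.

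**The letter and any reply form are not shown.** They may already invite a reason for declining. Their absence from an article is no fault in the plan, and no fault is claimed on that ground.

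**The Discussion promises a count and no more.** It gives no estimate of prevalence, sets no threshold, and does not say that a low count would show there is no barrier. Smartphone exclusion is not a progression trigger, and all data collected are to be considered. A reader might infer that this count alone decides whether the criterion stays; the document does not say so.

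What remains is that the stated recruitment order, the population counted and the stated use do not fit together unless the count is read as a lower bound, and the article does not say so.

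**Conclusion.** The point holds in a limited form. The number excluded for lack of a smartphone comes from telephone screening of people who have already shown interest. It misses non-owners who rule themselves out on reading the letter, except those who volunteer the reason as decliners. It is a lower bound and probably understates the barrier.

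The amount is not fixed by the document. With q = 22% it runs from no understatement of the share at k = 1, through 12.4% at k = 0.5, to 2.7% at k = 0.1, before allowing for decliners' reasons. The direction rests on one assumption, that people without a smartphone are less likely than owners to express interest in an app study. That is plausible but not documented.

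No primary criterion, sample size or analysis is affected. The point concerns one descriptive feasibility figure and the use the Discussion makes of it.

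**What to change.** Include a no-smartphone response with the invitation, which can be returned without taking part. If that is not practical, make it a fixed category when decliners are asked for reasons. If the invitation materials already offer this, only the reporting below needs to change.

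Report two figures side by side:
- the number stating that they have no smartphone, over all people invited;
- the number found ineligible on this criterion at the telephone screen, with the number screened as its denominator, labelled a lower bound.

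Reword the Discussion so that it says the screening count gives a minimum, and that both figures will be considered when access is reviewed for the definitive trial. The Background ownership figures can be quoted for context, with the caveat that they are national and for over-55s.

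The cost is one extra item and one extra count. Replies will still be incomplete, so the figure over all invited will also be a minimum, though likely a less severe one.
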